#### Population

The trial consists of 44 patients with a clinical diagnosis of RA based on The American College of Rheumatology (ACR)/The European League Against Rheumatism (EULAR) criteria.

#### Eligibility criteria

### Inclusion criteria

Patients are eligible to participate if they are aged 18-70; have a diagnosis of RA; report poor sleep quality (Pittsburgh Sleep Quality Index (PSQI) global score >5), have low disease activity score on 28 joints (DAS28) <3.2, have a normal 12-lead Electrocardiogram (ECG) and understand Danish.

### Exclusion criteria

Patients are excluded if they have documented sleep apnea (Apnea-Hypopnea Index (AHI) >15/hour); have night work during the period in which the intervention takes place; are pregnant or are breast-feeding, are being treated with steroids, hypnotics, antidepressants or antipsychotics, have cardiac symptoms corresponding to New York Heart Association (NYHA) Functional Classification >2; are regularly physically active (self-reported aerobic exercise >3 times per week).

#### Trial setting and recruitment

The patients are recruited from the Rheumatology outpatient clinics at two Copenhagen University Hospitals, Glostrup and Frederiksberg, in the Capital Region of Denmark. Potentially eligible patients receive written information by mail or are contacted in the outpatient clinics at Glostrup and Frederiksberg Hospital and receive a telephone call a few days later. If the patients are interested in participating in the trial, a telephone screening is conducted using the PSQI to clarify whether they fulfill the criteria for poor sleep (PSQI global score >5).

#### Screening

Eligible patients are screened for sleep apnea. This screening is performed by cardio-respiratory monitoring (CRM) consisting of electromyography of the tibialis anterior muscles, and electrocardiogram including channels of digital oximetry, nasal pressure and respiratory movements (Xtrace thoracic and abdominal straps). Patients with moderate to severe sleep apnea, AHI >15/hour, are excluded from the trial, and are referred to the Center for Sleep Medicine for treatment for sleep apnea.

Safety: During the screening period, to ensure that their health permits high-intensity intermittent aerobic training, the patients are asked, by means of a structured screening instrument, about their heart and lung function to ensure that they have no symptoms and no limitations on ordinary physical activity, e.g. shortness of breath when walking, climbing stairs etc. or mild shortness of breath and/or angina. Furthermore, the patients will have had an ECG taken to ensure the safety of participating in the aerobic intermittent training program.

#### Randomization and blinding

Included patients are randomly assigned to one of the two following conditions: aerobic intermittent training (n = 22) or control group (n = 22). Randomization is performed by computer-generated `random numbers´ with a 1:1 allocation ratio. Evaluation of primary outcome is performed by experienced polysomnographic technicians who are blinded to group allocation.

#### Intervention

The intervention consists of a total of 18 aerobic intermittent training sessions (20-30 minutes/session) spread over a maximum of eight weeks (2-3 times/week) as shown in Table 1. The training sessions are performed on bicycle ergometers (Kettler) and supervised by trained physiotherapists. Each session is initiated by a 5-minute warm-up period, followed by 4 blocks of 5-7.5 minutes alternating periods of continuous moderate intensity (40-50% watt max) and periods of intermittent high-intensity aerobic exercise (70-80% watt max) [38] and finally a 5-minute cool-down period. Exercise workload (watt) is determined individually by a watt max test at baseline, and calculated from the maximum load reached adjusted for the number of seconds performed at the highest load. The goal of the intervention is for each patient to attend at least 14 out of the 18 planned exercise sessions.

**Table 1 T1:** Exercise training program for patients randomized to 18 sessions of aerobic intermittent training

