**Methods/design:**

A randomized controlled trial including 44 patients with rheumatoid arthritis randomly assigned to an exercise training intervention or to a control group. The intervention consists of 18 session intermittent aerobic exercise training on a bicycle ergometer three times a week. Patients are evaluated according to objective changes in sleep as measured by polysomnography (primary outcome). Secondary outcomes include changes in subjective sleep quality and sleep disturbances, fatigue, pain, depressive symptoms, physical function, health-related quality of life and cardiorespiratory fitness.

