**18 sessions of aerobic intermittent training (6 – 8 weeks duration)**					
**Session 1 – 6**			**Session 7 - 18**		
Duration	20 minutes aerobic intermittent training including 5 minute warm-up and cool-down		Duration	30 minutes aerobic intermittent training including 5 minute warm-up and cool-down	
Bock 1 (5 min)	Continuous exercise	55-60% Wmax (70-80% HR)	Block 1 (7.5 min)	Continuous exercise	55-60% Wmax (70-80% HR)
Block 2 (5 min)	Intermittent training 3 x 60 -30 sec.	70-80% Wmax (80-90% HR)	Block 2 (7.5 min)	Intermittent training 4 x 60 -30 sec.	70-80% Wmax (80-90% HR)
Block 3 (5 min)	Intermittent training 3 x 60-30 sec.	70-80% Wmax (80-90% HR)	Block 3 (7.5 min)	Intermittent training 5 x 60 - 30 sec.	70-80% Wmax (80-90% HR)
Block 4 (5 min)	Continuous exercise	55-60% Wmax (70-80% HR)	Block 4 (7.5 min)	Continuous exercise	55-60% Wmax (70-80% HR)

Wmax = watt max, HR = Heart rate.

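### The exercise prescription contradicts itself on the intensity of the continuous blocks and on session length

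*Protocol article*

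**What the plan says.** All places are in the protocol article.

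- **Intensity, running text (Intervention).** The continuous periods are "continuous moderate intensity (40-50% watt max") and alternate with "periods of intermittent high-intensity aerobic exercise (70-80% watt max"). The section refers to Table 1 for the programme.
- **Intensity, Table 1.** Blocks 1 and 4 are the continuous ones. In sessions 1 to 6 and in sessions 7 to 18 they are set at "55-60% Wmax (70-80% HR"). Blocks 2 and 3 are the intermittent ones, at 70-80% of maximum watts.
- **Session length, running text.** There are "18 aerobic intermittent training sessions (20-30 minutes/session"). On structure: "Each session is initiated by a 5-minute warm-up period, followed by 4 blocks of 5-7.5 minutes", with a 5-minute cool-down at the end.
- **Session length, Table 1.** Sessions 1 to 6 are described as "20 minutes aerobic intermittent training including 5 minute warm-up and cool-down" and contain four 5-minute blocks. Sessions 7 to 18 carry the same description with 30 minutes and contain four blocks of 7.5 minutes.
- **Use of the prescription (Monitoring).** Changes from the prescribed wattage are noted for each session, and heart rate is noted for each block.

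**The concern.** In this trial the exercise dose is the intervention. For the continuous blocks the article gives two values that no single workload can satisfy, and one of them stands in the table that the text cites as its source. A physiotherapist who works from the text and one who works from the table would set the ergometer differently for half of the block time.

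Two things are at stake. First, the workload that patients are meant to receive is not defined, so the tested programme cannot be described or repeated exactly. Second, Monitoring records changes from a prescribed wattage, and the Discussion presents exact adherence, including watts, as a strength of the trial. Both need one reference value, and the continuous blocks have two. The session-length conflict adds that the stated duration cannot be the sum of the parts given for it.

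**Working it through.** **Intensity**

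| | Running text | Table 1 |
|---|---|---|
| Continuous blocks | 40-50% | 55-60% |
| Midpoint | (40 + 50)/2 = 45% | (55 + 60)/2 = 57.5% |
| Intermittent blocks | 70-80% | 70-80% |

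- Smallest gap between the ranges: 55 - 50 = 5 percentage points of maximum watts.
- Gap between midpoints: 57.5 - 45 = 12.5 points, a ratio of 57.5/45 = 1.28.
- The lower range cannot be read as recovery between intervals, because the text attaches it to the continuous periods.

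**Share of the programme affected** (two of four blocks)

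- Sessions 1 to 6: 2 × 5 = 10 of 20 block minutes.
- Sessions 7 to 18: 2 × 7.5 = 15 of 30 block minutes.
- Over 18 sessions: 6 × 10 + 12 × 15 = 240 of 6 × 20 + 12 × 30 = 480 block minutes, which is half.

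**Session length**

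The figures to reproduce are 20 and 30 minutes, with warm-up and cool-down included. Length = warm-up + 4 × block length + cool-down.

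| | Sessions 1-6 | Sessions 7-18 | Programme total |
|---|---|---|---|
| As labelled | 20 | 30 | 6 × 20 + 12 × 30 = 480 |
| Four blocks alone | 4 × 5 = 20 | 4 × 7.5 = 30 | 480 |
| Sum of the parts | 5 + 20 + 5 = 30 | 5 + 30 + 5 = 40 | 6 × 30 + 12 × 40 = 660 |

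The labelled lengths do not reproduce. They equal the blocks without warm-up and cool-down, and the parts give 660 - 480 = 180 minutes more (180/480 = 37.5%).

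Two readings that might reconcile the figures fail:

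- *Blocks 1 and 4 are the warm-up and cool-down.* The text places these before and after the four blocks, and in sessions 7 to 18 blocks 1 and 4 last 7.5 minutes, not 5.
- *The 5 minutes cover warm-up and cool-down together.* This gives 25 and 35 minutes, which still does not match.

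**Frequency and interval counts**

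- 18/3 = 6 weeks and 18/8 = 2.25 sessions per week, so a schedule averaging 2.25 to 3 per week fits 6 to 8 weeks.
- Reading the interval notation as 60 s plus 30 s: 3 × 90 s = 4.5 minutes in a 5-minute block, and 4 × 90 s = 6 minutes and 5 × 90 s = 7.5 minutes in 7.5-minute blocks. All of them fit.

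**The case against.** The strongest reply is that the core of the programme is consistent and that no planned analysis rests on the disputed values. Text and table agree on the 70-80% intervals, the block lengths, the 18 sessions and the eight-week limit. Under Statistical analyses, the per-protocol set is defined by attendance of at least 14 sessions, and the dose-response analysis uses cardiorespiratory fitness. Neither uses continuous-block intensity. Both disputed ranges also lie below the 70-80% given for the same sessions, so the conflict does not change the highest workload stated. All of this stands. It limits the consequences, but it does not remove the contradiction.

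A reader might infer more than the documents support:

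- **That two doses were delivered and the effect estimate mixes them.** Nothing in the article shows that some physiotherapists followed the text and others the table. The article permits this on intensity, but does not show that it happened. On duration, text and table carry the same labels and the same block lengths, so they do not define rival programmes. The label simply disagrees with its parts.
- **That block time could be 300 minutes instead of 480, a 60% difference.** The 300 comes from taking ten minutes off every labelled session (6 × 10 + 12 × 20). Both places state block lengths that total 480, so 300 is stated nowhere.
- **That weekly frequency is contradictory.** The abstract has "aerobic exercise training on a bicycle ergometer three times a week" and the Intervention section has "spread over a maximum of eight weeks (2-3 times/week"). Three lies within two to three. Only a steady two per week would need 18/2 = 9 weeks, and no section prescribes that.
- **That the interval counts are impossible.** Blocks 2 and 3 of sessions 7 to 18 hold four and five intervals in equal time. Nothing says that intervals must fill the block, and those of sessions 1 to 6 do not fill theirs either.

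**Conclusion.** The point holds for continuous-block intensity and for session length. The intensity conflict is the more serious: two disjoint ranges for the same blocks, 12.5 percentage points of maximum watts apart at the midpoints, over 240 of 480 block minutes. The session-length conflict is 20 and 30 minutes as labelled against 30 and 40 from the parts, or 480 against 660 minutes over the programme.

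The consequence is an undefined workload for half of the block time and no fixed reference for the recorded changes in intensity. The comparison of the randomised groups is not biased. Programme totals assume that all 18 sessions are completed as scheduled. The result needs no assumption from outside the article, and the article does not settle which of the conflicting values was intended.

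**What to change.** The investigators should:

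1. Reconcile the Intervention text and Table 1 into one intensity range for the continuous blocks and one session length that equals the sum of its parts. Which values are right is for them to decide.
2. Confirm the reconciled prescription to the physiotherapists who deliver the training.
3. State which version was used for any patients already trained. Trial status says that recruitment is under way, so this can still be established.
4. Use the reconciled version as the reference for recorded deviations in intensity.

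Two matters are tidying only: align the abstract's weekly frequency with that of the Intervention section, and explain the different interval counts in blocks 2 and 3 of sessions 7 to 18.

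The cost is a correction of text and table and a message to the training staff. No procedure, sample size or analysis changes.

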**18 sessions of aerobic intermittent training (6 – 8 weeks duration)**					
**Session 1 – 6**			**Session 7 - 18**		
Duration	20 minutes aerobic intermittent training including 5 minute warm-up and cool-down		Duration	30 minutes aerobic intermittent training including 5 minute warm-up and cool-down	
Bock 1 (5 min)	Continuous exercise	55-60% Wmax (70-80% HR)	Block 1 (7.5 min)	Continuous exercise	55-60% Wmax (70-80% HR)
Block 2 (5 min)	Intermittent training 3 x 60 -30 sec.	70-80% Wmax (80-90% HR)	Block 2 (7.5 min)	Intermittent training 4 x 60 -30 sec.	70-80% Wmax (80-90% HR)
Block 3 (5 min)	Intermittent training 3 x 60-30 sec.	70-80% Wmax (80-90% HR)	Block 3 (7.5 min)	Intermittent training 5 x 60 - 30 sec.	70-80% Wmax (80-90% HR)
Block 4 (5 min)	Continuous exercise	55-60% Wmax (70-80% HR)	Block 4 (7.5 min)	Continuous exercise	55-60% Wmax (70-80% HR)

Wmax = watt max, HR = Heart rate.

### Monitoring

For each exercise session any changes in the prescribed exercise intensity (watt) is noted. Patients’ heart rate (Polar) is monitored and noted for each training block, and the overall mean and maximum heart rate are registered after each session. In addition, the patients’ rated perceived exertion is recorded using the Borg Scale (6-20 rating).

#### Control group

The control group receives no exercise intervention during the test period and is encouraged to maintain a normal everyday life.

#### Trial endpoints

##### Data collection

Objective physiological as well as patient reported outcomes are collected at baseline and at the end of the intervention (6- 8 weeks).

### Assessment of primary endpoint

The primary outcome of the trial is changes in sleep as measured objectively by PSG at baseline and at the end of the intervention. PSG measurements are performed at the patient’s home in order for them to sleep in familiar surroundings. However, the primary investigator performs electrode placement and tests the equipment at Glostrup Hospital. Sleep monitoring is performed using Trackit™ Ambulatory EEG (Lifelines Ltd, [name]). The evaluation of the PSG measurements is performed following the guidelines of the American Academy of Sleep Medicine (AASM standard) 2007 [39].

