Against this background, the aim of this trial is to assess the efficacy of an aerobic intermittent exercise training intervention on sleep quality and sleep disturbances in patients with RA. The primary hypothesis is that intermittent aerobic exercise will be superior to no exercise in the improvement of objectively measured sleep. The secondary hypotheses are that patients randomly assigned to the exercise intervention will show greater improvement in subjective sleep quality and sleep disturbances, cardiorespiratory fitness, and physical function as well as reduced pain, fatigue and depressive symptoms and improved health-related quality of life compared to patients randomly assigned to the no-intervention (control group).

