#### Sample size

The sample size calculation is based on the sleep component `sleep efficiency´. A previous RCT [37], using PSG as measurement of sleep, examined the effect of a non-pharmacological intervention (cognitive behavioral therapy) on sleep disturbances in patients with insomnia and found a mean sleep efficiency of 81.4% (SD 7.4). The normal value for sleep efficiency is >85%. Thus the aim for the patients in the exercise intervention was to achieve a sleep efficiency of at least 86%. On this basis, and with a significance level of α = 5% and a power of 80%, it is estimated that 36 patients should take part in this trial. A drop-out rate of 20% is expected, which means that 44 patients are included, of which 22 are randomly assigned to the intervention group and 22 to the control group.

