### Statistical analyses

Continuous variables, i.e., sleep, cardiorespiratory fitness, physical function, pain, fatigue, depressive symptoms and health-related quality of life will be presented as either means with corresponding 95% confidence limits or as medians and interquartile range (IQR). The primary and secondary endpoints will be reported as a two-sample t-test comparing change scores in the two randomized groups. The primary outcome variables in the regression model will be sleep parameters. The regression model will allow control for the baseline value of the trial endpoints and other confounding variables that may impact changes in sleep parameters (e.g. age and gender). Categorical data, i.e., single questionnaire items, will be reported as proportions and compared across randomized groups using chi-squared tests or logistic regression. Significance level will be set at 0.05. All tests will be two-tailed. The primary analysis will compare changes in the intervention vs. the control group using the intention-to-treat principle including all available data. Missing observations will be handled according to the missing at random assumption. The secondary analysis will include only patients attending at least 14 exercise sessions (80%) out of the prescribed 18 (i.e. per protocol analysis). Finally, correlations will be performed to examine the dose-response relation between changes in the primary outcome (sleep) and cardiorespiratory fitness. Data entry will be undertaken using a secure web server and statistical analysis will be performed using Statistical Analysis Systems (SAS) version 9.3.

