## Discussion

The present trial will contribute with empirical evidence to the field of exercise and sleep that is currently characterized by premature empirical results but with significant potential as a non-pharmacological approach for improving sleep and with several aspects beneficial to health. The mechanisms of how physical exercise may reduce poor sleep are yet unknown. One hypothesis may be that sleep decrease symptoms of depression [48], another is that exercise engages with the two-process model of circadian and homeostatic regulation [49] or stimulates the restorative function during sleep and triggers an increase in body temperature [50,51]. The post-exercise drop in temperature may promote sleep onset latency and slow-wave sleep.

The present trial is superior to others within the field of exercise and sleep in three ways. Firstly, we have chosen the golden standard method for measuring sleep (i.e. PSG). In comparison, the majority of previous studies with the aim of improving sleep through physical exercise interventions have relied on self-reported instruments such as PSQI and only one trial has used polysomnographic assessment to measure sleep objectively [35].

Secondly, whereas current exercise trials typically apply continuous moderate intensity aerobic exercise training, we have chosen to apply aerobic intermittent training. While regular continuous aerobic exercise is known to improve a wide range of health outcomes, including cardiorespiratory fitness in both healthy people and clinical populations, aerobic intermittent training of shorter duration may result in an equal or superior improvement in fitness [36].

Finally, this is the first trial within the field of RA to evaluate the effect of aerobic intermittent training on improvement in sleep quality and sleep disturbances. The detailed information collected in this trial regarding the exact completed adherence to the exercise regime (including intensity (watt) as well as pulse monitoring during each training block and interval, and objective measured sleep duration, sleep stages, and sleep quality) is expected to provide important experimental results that can contribute with evidence of both aerobic intermittent training and poor sleep, including causal interactions between the two.

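### The primary outcome is left as sleep or sleep parameters at one unadjusted 0.05 level, while the trial is sized on sleep efficiency alone

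*Protocol article*

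**What the plan says.** - **Endpoint.** The protocol article, under Assessment of primary endpoint, states: "The primary outcome of the trial is changes in sleep as measured objectively by PSG". The Design section and the Abstract are equally general. None of them names a PSG variable.
- **Hypothesis.** The Background says that "intermittent aerobic exercise will be superior to no exercise in the improvement of objectively measured sleep". It names no variable either.
- **Analysis.** Statistical analyses uses the plural: "The primary outcome variables in the regression model will be sleep parameters". It then sets the level, "Significance level will be set at 0.05", and adds "All tests will be two-tailed". It shows no ordering, alpha split or success rule.
- **Sizing.** Under Sample size: "The sample size calculation is based on the sleep component" sleep efficiency. The paragraph contrasts a reference mean of 81.4% (SD 7.4) with a target of at least 86%, at alpha 5% and 80% power.
- **Other objective measures.** The Discussion says the trial collects "objective measured sleep duration, sleep stages, and sleep quality".
- **Secondary outcomes.** The secondary outcomes in the Abstract, the Background and the secondary endpoint section include no PSG variable.

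**The concern.** Four places define the primary outcome (Abstract, Background hypothesis, Design, Assessment of primary endpoint), and none says which PSG variable decides the trial. The analysis section makes the primary variables plural. Since no PSG variable is listed as secondary, every PSG variable falls under primary by default.

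Two things are at stake. First, a significant result in any one PSG variable could be presented as meeting the primary hypothesis, and the 5% error rate would then not describe that claim. Second, the 80% power statement concerns sleep efficiency only, so it does not describe a test of sleep parameters in general.

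**Working it through.** **1. The plan's own figures.** The stated error rate is 0.05, which is correct for one two-sided test of one variable. The stated size is 36 before drop-out, for sleep efficiency, with difference 86 − 81.4 = 4.6 and SD 7.4. The usual two-sample formula gives, per arm,

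2 × 7.4² × (1.960 + 0.842)² / 4.6² = 40.6, so 41 per arm and 82 in total.

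The figure of 36 is therefore not reproduced. That is a separate matter and the present point does not depend on it. It bears only on the choice of remedy (step 5).

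**2. Inputs for the error rate.** The level of 0.05, two-sided, is from Statistical analyses. The number of primary PSG variables, k, and their correlation, ρ, are not in the document. Both are assumptions below. The objective sleep variables that the article ties to this trial are sleep efficiency (Sample size) and sleep duration, sleep stages and sleep quality (Discussion). None is listed as primary, so k cannot be counted.

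**3. Chance of at least one false positive, each variable tested at two-sided 0.05.** Under independence this is 1 − 0.95^k. For correlated variables it was simulated with equally correlated normal test statistics (at least 300,000 draws).

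| k (assumed) | independent | ρ = 0.3 | ρ = 0.5 |
|---|---|---|---|
| 1 | 0.05 | – | – |
| 2 | 1 − 0.95² = 0.0975 | 0.0950 | 0.0909 |
| 3 | 1 − 0.95³ = 0.1426 | 0.1354 | 0.1258 |
| 6 | 1 − 0.95⁶ = 0.2649 | 0.241 | 0.207 |

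Strong correlation reduces the excess but does not remove it. At ρ = 0.9 the values are 0.0706 for k = 2 and 0.0833 for k = 3.

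**4. Counting only favourable results.** The hypothesis is one of improvement. Where the favourable direction is clear, only the favourable half of each two-sided test, 0.025, can confirm it falsely. Under independence this gives 1 − 0.975^k:

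- k = 1: 0.025
- k = 2: 1 − 0.975² = 0.049
- k = 3: 1 − 0.975³ = 0.073
- k = 6: 1 − 0.975⁶ = 0.141

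**5. Cost of keeping several primary variables.** With a Bonferroni level of 0.05/k and the article's own difference and SD, the formula in step 1 gives 100 patients in total for k = 2 and 110 for k = 3, before drop-out. At 18 per arm, power for sleep efficiency would be about 35% and 30%, against about 46% at an unsplit 0.05. A single primary variable carries no such penalty.

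**The case against.** The best defence is that the article points to one variable. It sizes the trial on sleep efficiency, sets a target value for it, and uses the singular for the primary endpoint in Design and in Assessment of primary endpoint. The plural occurs in a sentence about the regression model and may be loose drafting. A multiplicity procedure could also sit in an analysis plan or full protocol that is not shown. It stands that a procedure missing from a journal article is no fault. It does not settle the naming: the choice of primary variable belongs in the endpoint section, and neither that section nor the analysis section commits to sleep efficiency.

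Three stronger readings are tempting, and the document does not support them.

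- **That the plan lays down a rule of testing each variable at 0.05, with any one success sufficient.** It gives one significance level and no success rule. Testing each at 0.05 is an inference, though the natural one from plural primary variables and a single unadjusted level.
- **That the article lists six or more PSG endpoints, so that 26% is its error rate.** Awakenings appear in another trial's results and in this trial's self-reported diary. Sleep onset latency and slow-wave sleep appear in the Discussion as possible mechanism, and latency otherwise only as a questionnaire component. Six is an illustration.
- **That the whole two-sided figure is false confirmation of the hypothesis.** A significant worsening in sleep efficiency or duration would not confirm improvement, so step 4 is the fairer count where direction is clear. Sleep stages are less clear-cut.

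**Conclusion.** The point holds as an inconsistency between the endpoint and analysis sections, which leave the primary variable open and plural, and the sample size section, which rests on one variable. It decides what may be reported as trial success, so it is more than missing detail.

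That the error rate exceeds 5% is firm for any two or more imperfectly correlated variables each tested at 0.05 as primary. By how much is not known. The range runs from about 9 to 10% for two variables, through 13 to 14% for three, to 21 to 26% for six (correlation 0.5 to independence). Counting favourable results only, six independent tests give about 14%, against 2.5% for one. All of these rest on an assumed number of variables, an assumed correlation and the inferred reading that each is tested at 0.05. Confidence is high on the naming gap and limited on the magnitude.

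**What to change.** In Design, Assessment of primary endpoint and Statistical analyses, name the between-group difference in change in PSG sleep efficiency, the variable the trial is sized on, as the single primary endpoint, tested at two-sided 0.05. List all other PSG variables as secondary or exploratory, reported with confidence intervals and without a primary claim. The planned comparison of change scores can stay as it is for this purpose; how to adjust for baseline is a separate question.

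The trial is registered and the article reports that recruitment is under way. The change should therefore be a dated amendment, with the registry entry brought into line, before any between-group comparison of outcomes.

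Cost: no new data and no loss of alpha, but an amendment is needed, and a result in another PSG variable can no longer be claimed as primary. If several variables must stay primary, they should be listed with a success rule and a multiplicity procedure, and the trial sized for it, at the price shown in step 5 of the working.
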